### Methods: monitoring

#### Data monitoring

##### Formal committee

A Data Monitoring Committee (DMC) has been established. The DMC is composed of two cardiologists, one cardiac surgeon, and one cardiac anesthesiologist who are not involved in the study and not participating in the care of enrolled patients. Reports will be made available after every 50 patients that are accrued.

##### Interim analyses

Interim analyses will be performed after enrollment of the first and second 100 consecutive patients. Results from interim analyses will be reported to the DMC and the medical monitor (a cardiac anesthesiologist not participating in the study or the care of the patients). The principal investigator (PI) will be blinded to these results. Using the Haybittle-Peto rule for efficacy analysis, a difference of at least four standard deviations for the first interim analysis and three standard deviations at the interim analysis in the incidence of the primary outcome will justify premature halting of the study. In order to be considered significant, the corresponding chi-square value is 16 (*α* = 0.001).

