#### Sample size

Two groups are necessary for this trial: the control group and the intervention group. Based on analysis performed on our aortic surgery database for the years 2012 and 2013, the incidence of POAF in cardiac surgery patients was calculated to be 37.6%. A thorough study of the academic literature, including a meta-analysis of similar studies [10] shows that intervention reduces atrial fibrillation incidence by 50%. Therefore, an atrial fibrillation incidence of 40% in the control group with a proposed decrease of 50% with intervention requires a total of 158 subjects at 80% power and 0.05 alpha. Should the incidence of atrial fibrillation be 30% in the control with a hypothesized 50% decrease, a total of 322 subjects would be required at 90% power. In order to remain conservative, account for 5% protocol violation and 10% loss to follow-up/dropout, and retain power, a total sample size of 350 (175 patients in each treatment group) will be sufficient for this study. Should the incidence of POAF be lower than expected at interim analysis, sample size calculations will be re-estimated to ensure sufficient power at the time of analysis.

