#### Data management

##### Statistical methods

Pre-operative differences between the control and the intervention group will be assessed by univariate analysis. Continuous variables will be analyzed by way of Student’s *t* test or the Mann-Whitney *U* test and categorical variables will be analyzed by use of the chi-squared test. Postoperative differences, including atrial fibrillation and other complications, will also be assessed between the control and intervention groups by way of univariate analysis.

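### The efficacy stopping boundary is given as 3 SD, chi-square 16 and alpha 0.001, which do not agree, so the second interim has no determinate threshold

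*Protocol article*

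**What the plan says.** The protocol article, Interim analyses, schedules two looks: "Interim analyses will be performed after enrollment of the first and second 100 consecutive patients". The boundary is then stated in standard deviations, under a Haybittle-Peto rule. The first look needs a difference of 4 SD or more. For the other look the section says: "three standard deviations at the interim analysis in the incidence of the primary outcome will justify premature halting of the study". That part does not name its look, but by elimination it is the one at 200 patients.

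The next sentence restates the criterion on the chi-square scale: "In order to be considered significant, the corresponding chi-square value is 16", followed in parentheses by alpha = 0.001. It gives one value, does not say which look it governs, and does not say whether alpha is one- or two-sided. Nothing elsewhere in the article settles which figure applies at the second look.

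**The concern.** The section offers three ways to express one boundary: a number of standard deviations, a chi-square value and an alpha. For a two-group comparison of a proportion these are transformations of each other, so they must agree. Here chi-square 16 matches only the four-SD look, and the alpha printed beside it matches neither look.

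This is the only efficacy rule the article gives the Data Monitoring Committee. If the second-look result falls between the stated thresholds, one sentence justifies halting and the next says the result is not significant. The committee would then have to choose a boundary after seeing comparative data, which is what a pre-specified boundary is meant to prevent.

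**Working it through.** **Inputs**
- Boundaries: 4 SD at the first look, 3 SD at the second, chi-square 16, alpha 0.001 (Interim analyses).
- Looks at 100 and 200 patients (Interim analyses). With 1:1 allocation this is about 50 and 100 per arm.
- Design effects (Sample size): 40% versus 20% ("with a proposed decrease of 50% with intervention requires a total of 158 subjects at 80% power and 0.05 alpha") and 30% versus 15% ("a total of 322 subjects would be required at 90% power"). Planned total 350, 175 per arm.
- Test: "categorical variables will be analyzed by use of the chi-squared test" (Statistical methods). A 2×2 table has 1 df.

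**Step 1. Try to reproduce the stated pair, chi-square 16 with alpha = 0.001.** On 1 df, chi-square = z².

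| Stated as | z | Chi-square | Two-sided p | One-sided p |
|---|---|---|---|---|
| 4 SD | 4.00 | 16.00 | 0.000063 | 0.000032 |
| 3 SD | 3.00 | 9.00 | 0.0027 | 0.00135 |
| alpha 0.001, two-sided | 3.29 | 10.83 | 0.001 | – |
| alpha 0.001, one-sided | 3.09 | 9.55 | – | 0.001 |

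The pair does not reproduce. Chi-square 16 has a two-sided p about 16 times smaller than the label (0.001 / 0.000063 ≈ 16). On 3 df it would have p = 0.0011, but this comparison has 1 df.

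**Step 2. Example tables at the second look (100 per arm).** Without continuity correction, chi-square = N(ad − bc)² / (n₁n₂ × events × non-events).

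For 40 versus 20 events: 200 × (40×80 − 20×60)² / (100 × 100 × 60 × 140) = 200 × 2000² / 84,000,000 = 9.52, so z = 3.09.

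| Events, control vs intervention | Chi-square | Two-sided p | 3 SD | alpha 0.001 (two-sided) | Chi-square 16 |
|---|---|---|---|---|---|
| 40 vs 21 | 8.52 | 0.0035 | continue | continue | continue |
| 40 vs 20 | 9.52 | 0.0020 | stop | continue | continue |
| 40 vs 19 | 10.60 | 0.0011 | stop | continue | continue |
| 40 vs 18 | 11.75 | 0.0006 | stop | stop | continue |
| 40 vs 15 | 15.67 | 0.00008 | stop | stop | continue |
| 40 vs 14 | 17.15 | 0.00003 | stop | stop | stop |

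With 40 control events, stopping therefore needs at most 20, 18 or 14 intervention events, depending on the sentence applied.

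**Step 3. How likely is a conflict?** Exact binomial enumeration at 100 per arm:

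| True rates | P(chi-square ≥ 9) | P(≥ 10.83) | P(≥ 16) | P(between 9 and 16) |
|---|---|---|---|---|
| 40% vs 20% | 0.544 | 0.418 | 0.176 | 0.368 |
| 30% vs 15% | 0.322 | 0.220 | 0.064 | 0.258 |

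**Step 4. Overall type I error.** Looks at 100, 200 and 350 patients, final test at |z| ≥ 1.96, by numerical integration of the joint normal distribution of the three statistics:
- 4 SD then 3 SD: 0.0506
- 3.29 SD at both looks: 0.0507
- 4 SD at both looks: 0.0500

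**The case against.** The strongest reply is that the operative rule is the sentence in standard deviations, which is specific to each look, and that chi-square 16, being exactly four squared, only glosses the first look. The second look would then simply be 3 SD. This is possible, and the direct 9-versus-16 clash does depend on reading the last sentence as applying to both looks. But the sentence has no such limit, and its plain meaning is general. Even on the narrow reading, alpha = 0.001 is wrong for chi-square 16, and the section remains inconsistent.

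The alpha may also be loose shorthand for 3 SD taken one-sided (0.00135, which rounds to 0.001). If so, it is attached to the wrong chi-square value, and no sidedness is stated.

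Two points limit the emphasis and stand:
- The expected second-look result lies between the thresholds only for 40% versus 20%. Under 30% versus 15%, the scenario behind the 322 subjects and the larger total, 30 versus 15 events gives chi-square 6.45, which means continue on every reading. A conflict is still far from rare there, at 26%.
- Type I error is hardly affected by the choice.

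Leaving detail to a fuller document is no defence, because the article prints explicit numbers that contradict each other.

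**Conclusion.** The concern holds. No reading makes the stated figures agree: chi-square 16 is not alpha 0.001 on either sidedness, neither look has alpha 0.001, and the article does not settle which threshold governs the second look. Under the trial's own assumptions, the chance that the second look lands where the sentences disagree is 37% (40% versus 20%) or 26% (30% versus 15%). These figures assume equal allocation, outcomes known for all 200 patients and an uncorrected chi-square test. The consequence is an indeterminate decision on stopping for efficacy, with overall type I error close to 0.05 on each version. The rule should be corrected before the first interim analysis.

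**What to change.** Replace the chi-square sentence with one set of matching values per look, and name the second interim explicitly:
- First interim (100 patients): |z| ≥ 4, chi-square ≥ 16, two-sided p ≤ 0.00006.
- Second interim (200 patients): |z| ≥ 3, chi-square ≥ 9, two-sided p ≤ 0.0027.

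Delete the alpha = 0.001 label. If a uniform two-sided 0.001 was intended, state chi-square ≥ 10.83 at both looks and drop the 4 SD and 3 SD wording.

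In either case the final test can stay at two-sided 0.05, with the overall type I error stated (about 5.1% for looks at 100, 200 and 350). That figure assumes a final total of 350. The Sample size section allows re-estimation at interim, so it should be recalculated if the total changes.

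The cost is one sentence in the protocol, and the same wording in the committee's charter if it repeats the rule. It needs no extra patients and no extra analyses.

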##### Harms

Serious adverse events (SAE) will be reported to the DMC, the Institutional Review Board and the PI. The study will be interrupted in case of significant differences between groups at interim analyses in terms of SAE during the hospitalization. In cases of mortality, if it is determined that death was a direct result of the trial intervention, the study will be stopped. A subject may be removed from the study if, during the time of surgery, the attending surgeon determines that it would be unsafe to perform the posterior left pericardiotomy due to unexpected difficulty during surgery, additional cardiac surgery, extended cardiac ischemic time, or hemodynamic instability. Removed patients will continue to receive the same care had they not been enrolled. The removed patient will be replaced in the trial should this occur before randomization. The results of the patient will not be included in the dataset or analysis. Since the primary analysis is based on ITT then the patient will be included in the analysis if they are already randomized.

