#### Participant timeline

The main outcome of interest is the occurrence of POAF after cardiac surgery. Patients will first be screened for eligibility and willingness to participate in the trial. Then, informed consent will be collected from participating patients, who will be randomized into one of the two study groups. Postoperatively, patients will be closely monitored for the occurrence of atrial fibrillation, pleural and pericardial effusions. Times of event and to discharge will also be assessed. These outcomes will be monitored until the time of the follow-up visit, which will be within 30 days postoperatively for the majority of patients at our institution. Participation until this time point represents complete participation in the trial. We intend to include only patients who have completed follow-up (Fig. 2).

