In a previous meta-analysis by Kaleda et al., posterior pericardiotomy was found to significantly reduce the incidence of POAF. This study showed a substantial reduction in total arrhythmias and atrial fibrillation in the posterior pericardiotomy group (odds ratio 0.31 and 0.33, respectively). The reported number needed to treat was six patients to prevent one case of atrial fibrillation. However, this meta-analysis was non-conclusive as it was based on seven studies which were either cohort or non-blinded studies. In addition, the outcomes assessed were not homogenous, with primary outcome measures varying between the incidence of postoperative pericardial effusions, arrhythmias or atrial fibrillation [6]. In 1999, Kurlay et al. reported the results of a randomized controlled trial. In 200 patients, atrial fibrillation rate (6%) was significantly lower in the posterior pericardiotomy group in comparison with the control group (34%) (*p* < 0.001). In the control group, early and late pericardial effusion rates were 54% and 21%, respectively, in contrast to that of the posterior pericardiotomy group which was zero for both (*p* < 0.001). Delayed pericardial tamponade was also significantly lower in group I (0% vs. 10%; *p* = 0.001). However, in this trial, patients receiving beta-blockers were excluded and, therefore, its results are not relevant to current practice [7]. In a more recent randomized trial, similar methodology was utilized with promising results in 50 posterior pericardiotomy patients. POAF was significantly lower in the posterior pericardiotomy group compared with the control group (10% vs. 30%, *p* < 0.010). Perioperative pericardial effusion rate was 12% compared to 42% in the control group (*p* < 0.001). The overall incidence of total arrhythmias in patients with early pericardial effusion was significantly higher than in those without this complication (18 vs. 9 patients) [8].

The present randomized study should significantly contribute to the assessment of the role of posterior pericardiotomy to reduce the incidence of atrial fibrillation after cardiac surgery.

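### The between-group SAE stopping comparison ends at discharge, while the trial's safety follow-up runs to the clinic visit, so non-fatal SAEs after discharge cannot count in it in either arm

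*Protocol article*

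**What the plan says.** All references are to the protocol article.

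- **Harms.** The comparison that can interrupt the trial is worded: "The study will be interrupted in case of significant differences between groups at interim analyses in terms of SAE during the hospitalization". Two further provisions carry no stated time window: "Serious adverse events (SAE) will be reported to the DMC, the Institutional Review Board and the PI", and "In cases of mortality, if it is determined that death was a direct result of the trial intervention, the study will be stopped".
- **Interim analyses.** "Interim analyses will be performed after enrollment of the first and second 100 consecutive patients". Under Formal committee, the Data Monitoring Committee (DMC) also receives a report for every 50 patients accrued.
- **Participant timeline.** "Postoperatively, patients will be closely monitored for the occurrence of atrial fibrillation, pleural and pericardial effusions". Then: "These outcomes will be monitored until the time of the follow-up visit, which will be within 30 days postoperatively for the majority of patients". The Abstract places the visit 15 to 30 days after surgery.
- **Concomitant care.** An echocardiogram is done before discharge and again at the follow-up visit. Patients who leave with a moderate or larger pleural effusion have a chest film in clinic 2 to 3 weeks after discharge.
- **Outcomes.** Left pleural effusion, pericardial effusion, major adverse events and death are the safety outcomes. None is limited to the hospital stay.
- **Data collection methods.** Collection is described from enrolment through the hospital stay.
- **Discussion.** On an earlier randomized trial of 200 patients: "In the control group, early and late pericardial effusion rates were 54% and 21%, respectively", with zero for both after pericardiotomy. On tamponade: "Delayed pericardial tamponade was also significantly lower in group I (0% vs. 10%; *p* = 0.001".

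**The concern.** The trial tests an added surgical step. The Background names more left-sided pleural effusion as a complication specific to that step, and the Discussion adds prolonged drainage of such effusions. These problems need not be over at discharge, and Concomitant care expects some patients to go home with a moderate or larger effusion. The stopping comparison nevertheless closes when the patient leaves hospital.

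A truncated comparison can mislead in either direction. An excess of non-fatal SAEs after discharge in the pericardiotomy arm could not trigger it. Conversely, an early in-hospital excess in that arm could interrupt the trial while later control-arm events that would offset it, such as delayed tamponade, stay uncounted.

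There is also a smaller point. Length of stay is a secondary outcome that the intervention is hoped to change. A window that ends at discharge may therefore differ in length between the arms, which a window tied to the follow-up visit largely avoids.

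**Working it through.** **1. The windows side by side**

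| Item | Window stated | Section |
|---|---|---|
| Between-group SAE comparison that can interrupt the study | Hospital stay only | Harms |
| SAE reports to the DMC, ethics board and principal investigator | None stated | Harms |
| Stop for a death directly due to the intervention | None stated | Harms |
| Pleural and pericardial effusion | To the follow-up visit | Abstract, Participant timeline |
| Echocardiogram for pericardial effusion | Before discharge and at the visit | Concomitant care |
| Major adverse events, death as safety outcomes | No in-hospital limit | Outcomes |

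The first row is the only stated between-group SAE comparison and the only row cut at discharge. A non-fatal SAE after discharge therefore cannot enter it.

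**2. Uncounted time that needs no assumption**

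For patients discharged with a moderate or larger pleural effusion, the clinic film comes 2 to 3 weeks after discharge: 2 × 7 = 14 to 3 × 7 = 21 days outside the rule.

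**3. The cited tamponade figure**

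Assuming equal arms, 0/100 against 10/100 gives a Pearson chi-square of 10.53, p = 0.0012 (Fisher p = 0.0015). This agrees with the quoted p = 0.001. The figure is sound as cited; what it can support is taken up under the objection.

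**4. Illustration of lost sensitivity**

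The article gives no SAE rate, no test level and no in-hospital share of events. Assumptions: a true SAE difference of 10% against 0% through the visit, in either direction; a two-sided Fisher test at 0.05; and a fraction f of the events in hospital. With no events in one arm, significance needs at least 6 in the other:

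- 50 per arm: 5 v 0 gives 2 × C(50,5)/C(100,5) = 0.056; 6 v 0 gives 2 × C(50,6)/C(100,6) = 0.027.
- 100 per arm: 5 v 0 gives 2 × C(100,5)/C(200,5) = 0.059; 6 v 0 gives 2 × C(100,6)/C(200,6) = 0.029.

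The chance of a significant result is P(X ≥ 6), with X binomial (n, 0.10 × f):

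| f counted | First look, 50 per arm | Second look, 100 per arm |
|---|---|---|
| 0 | 0% | 0% |
| 0.25 | 0.2% | 4% |
| 0.5 | 4% | 38% |
| 0.75 | 17% | 77% |
| 1 | 38% | 94% |

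The row f = 1 assumes that every patient at the look has completed the visit. The table shows how strongly the rule depends on f, not what f is.

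**5. Follow-up still open at a look**

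The looks are triggered by enrolment. The article implies recruitment of 350 patients over 12 months (Trial status), 18 months or 24 months (Recruitment). With even accrual, one month's intake is 350/12 = 29, 350/18 = 19 or 350/24 = 15 patients. So at the 100th enrolment about 71 to 85 patients would be at least a month past enrolment, and at the 200th about 171 to 185.

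**The case against.** **A hospital window is a defensible early trigger.** Surveillance in hospital is uniform, with continuous monitoring and daily chest films. The window is also nearly complete at each look, whereas 15 to 29 recent patients would lack the visit. This stands as a reason to keep the in-hospital comparison. It is not a reason to have no other.

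**Other safeguards exist.** A reader might infer that harm after discharge escapes all oversight. It does not. SAE reporting and the death rule have no stated time limit, and the DMC receives reports every 50 patients. What remains is that none of these is stated to compare non-fatal SAEs after discharge between the arms.

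**The cited late events are not harm from pericardiotomy.** A reader might infer from the 21% and 10% that the document shows late harm from the procedure. Both are control-arm rates in an earlier trial, with 0% after pericardiotomy. Late and delayed are not defined as after discharge, and early effusion (54%) was more frequent than late. The Discussion itself calls that trial's results not relevant to current practice, because patients on beta-blockers were excluded. The figures show only that such events can occur late. For the intervention, the Discussion names prolonged pleural drainage without a rate or timing.

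**The later data may not all be collected.** It is tempting to say that the fuller comparison needs only wording. Participant timeline follows atrial fibrillation and effusions to the visit, not SAEs in general. Data collection methods speaks of the hospital stay, and clinic chest films are limited to some patients. This objection stands and adds to the cost of the fix.

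**Conclusion.** The point holds as a mismatch of windows. The one between-group SAE comparison that can interrupt the trial leaves out non-fatal SAEs after discharge in both arms, although effusions are followed to the visit and the other safety outcomes have no in-hospital limit. This rests on the wording alone.

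The size cannot be derived: neither the SAE rate nor the share of SAEs after discharge is given. Under the illustrative assumptions, the chance of detecting a 10% against 0% difference at the second look runs from 0% (all events after discharge) to 94% (all counted). Any share of follow-up time covered by the rule would rest on an assumed length of stay, and would be a share of time, not of events.

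No figure stated in the article is wrong because of this, and the primary analysis is unaffected. It is a cheap improvement to safety monitoring, not evidence that pericardiotomy does late harm.

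**What to change.** In Harms, define the between-group comparison as SAEs from surgery through the follow-up visit, including readmissions. At each interim look, present two comparisons:

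- in-hospital SAEs for all patients, as now, so that nothing is delayed;
- SAEs through the visit for patients who have reached it or died.

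In Data collection methods, state that SAEs and readmissions since discharge are recorded at the visit for every patient.

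**Cost.** The visit is already planned, so the added work is confirming SAE and readmission capture there. The complete comparison for a given look lags it by up to about 30 days.

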### Methods: ethics and dissemination

#### Research ethics approval

The study was approved by the Institutional Review Board on 26 May 2016: Protocol number 1502015867R001.

#### Consent or assent

Consent is required prior to individual patient enrollment according to institutional guidelines. Research will be performed according to the Declaration of Helsinki.

#### Ancillary studies

All of the patients in the study will have a pre-bypass and post-bypass TEE examination performed. Pre-operative and perioperative diastolic dysfunction in cardiac patients has been shown to be predictor of poorer outcomes. Ashes et al. demonstrated a higher incidence of POAF in CABG patients with worsening diastolic function perioperatively compared to patients with unchanged or improved diastolic function [12]. Other studies have shown that pre-operative diastolic dysfunction predicted higher incidence of POAF in cardiac surgical patients. Our primary objective is to evaluate whether or not worsening RV systolic or diastolic function affects the rate of POAF. Additionally, we hypothesize that the posterior pericardiotomy may affect atrial filling, as measured by the pulmonary venous flow and left atrial contraction indices and the diastolic filling patterns of the LV.

Echo images will be taken before sternotomy and after chest closure to assess for left and RV diastolic dysfunction, and well as left atrial filling indices. These images will be taken as part of the routine TEE examination, but at the time points specified above to minimize acute hemodynamic and volume changes.

Specific measurements to be recorded are the transmitral flow (mitral E and A waves, A duration, deceleration time), pulmonary venous flow (S and D waves and A duration), left atrial appendage velocities, tissue Doppler of the LV wall (medial and lateral e’), the RV fractional area of change (FAC), the hepatic venous flow (S, D, and A waves), and the transtricupsid flow (tricuspid E and A waves). These measurements will be taken offline and are part of the standard examination and American Society of Echocardiography (ASE) guidelines on quantification of LV diastolic dysfunction [13, 14]. Post-processing measurements will also be taken of RV and LV strain to assess whether a change in strain is predictive of POAF. Echocardiographers will be blinded to the intervention unless there is a complication that requires anesthetic intervention that is unique to having a posterior pericardiotomy.

